### Outcomes

Our primary evaluation of treatment efficacy is the reduction of observer-rated PTSD symptom severity, operationalised as a reduction CAPS-5 severity scores. Secondary objectives include evaluation of NAC to reduce self-reported symptoms of (1) PTSD, (2) depression and anxiety, (3) substance use, (4) craving and (5) somatic symptoms. Evaluation of treatment efficacy will be assessed over the entire trial period. Retention of treatment effects will be assessed at weeks 16 and 64 post-randomisation. The safety and tolerability of the intervention will be evaluated by self-report.

Participants may elect to provide a blood sample at baseline and Week 12 assessments. Blood based biomarkers of oxidative stress will be evaluated as exploratory outcomes. Blood analysis will include measurement of IL-6 (interleukin-6), TNF-alpha (tumour necrosis factor alpha), TBARS (thiobarbituric acid reactive substances), MDA (malondialdehyde) and BDNF (brain-derived neurotrophic factor). Modulation of these blood-based proteins will be correlated with treatment response. Participants will not be fasting prior to the blood collection. BD vacutainer SST II advance tubes (5 mL) will be used to collect the sample and then allowed to rest for 30 min prior to being centrifuged at 1300 g for 15 mins. The supernatant (serum) will be extracted and aliquoted into 2 × 1.8 ml tubes. All samples will be stored at − 80 degrees Celsius until tested.

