**Discussion:**

This is the first multicentre, double blind, randomised, placebo-controlled trial of adjunctive NAC for treatment-resistant PTSD. NAC has an established safety profile, is readily available and easy to administer, and has a favourable tolerability profile, therefore making it an attractive adjunctive therapy. Inclusion of blood analyses to assess potential target engagement biomarkers of oxidative stress and neuroinflammation may help gauge the biological mechanisms of effect of NAC.

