### Sample size calculation and recruitment target

The target sample size is 126 participants (63 per arm). For a two-tailed analysis with alpha = 0.05, beta = 0.2, the study is powered at 80% to detect a true difference in CAPS-5 scores between the NAC and placebo groups of 10+/− 20 points. In our pilot trial, effect sizes for PTSD symptoms as well as all secondary measures exceeded this threshold. Using a conservative attrition rate of one-third, we will need to recruit 190 participants to have 126 complete the trial and follow-up.

The study aims to recruit participants referred by their treating clinician or self-referred from the community. A summary of the participant flow through the study is shown in Fig. 1.

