**Secondary Outcomes**											
*Depression & Anxiety*	**HADS** (14 item self-report screening measure of anxiety and depression, designed for use in medical settings) [31]	X		X		X		X		X	X
	**HAM-D** (17 item observer rated scale; evaluates core symptoms of depression) [32]										
*Self-rated PTSD symptoms*	**PCL-5** (20 item self-report measure of PTSD symptoms) [33]	X	X	X	X	X	X	X	X	X	X
*Somatic symptoms*	**PHQ-15** (15 item self-report measure of degree to which one has been bothered by somatic symptoms over the past month) [34]	X		X		X		X		X	X
*Quality of life*	**WHO-QOL BREV** (26 item measure of subjective quality of life) [35]	X		X		X		X		X	X
*Alcohol use*	**AUDIT** (Participant answer ten-items relating to frequency of symptoms and behaviours associated with alcohol misuse) [36]	X		X		X		X		X	X
*Substance craving*	**Visual Analogue Scale** (to assess substance craving over the past week. Participants will rate 5 items using anchors of 0 (“not at all”) to 10 (“extreme” or “all the time”)	X		X		X		X		X	X
*Biomarkers of oxidative stress*	**Optional blood analysis** (IL-6, TNF-alpha, TBARS, MDA, BDNF)	X						X			

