While NAC has been implicated as an effective adjunctive treatment for many psychiatric conditions, the mechanism of effect has not yet been fully elucidated. The therapeutic effects of NAC are likely mediated via its ability to modulate numerous pathophysiological processes including oxidative stress, neurogenesis and apoptosis, mitochondrial dysfunction, neuroinflammation and dysregulation of glutamate and dopamine [26]. Determining the underlying mechanisms of NAC in PTSD is helpful, not only to understanding the underlying neurobiology of the illness but to discover additional therapies that may operate on similar pathophysiological pathways. Of key interest in the current study is NAC’s ability to replenish glutathione and thereby diminish oxidative stress and neuroinflammation, which are well established biomechanisms in PTSD and its other psychiatric comorbidities [16–18]. While studies have speculated on the mechanisms of action of NAC on psychiatric symptoms [26, 40] few have directly assessed blood-based biomarkers of oxidative stress and neuroinflammation in the context of treatment with NAC. The inclusion of blood-based biomarkers of oxidative stress and neuroinflammation is therefore a key methodological advantage of the present study.

A final advantage for this study is the heterogeneity of the sample. The broad inclusion and limited exclusion criteria mean that participants experiencing a range of psychiatric comorbidities will be eligible, and the adjuvant approach means that it will be available to most individuals with PTSD. To overcome the lack of specificity incurred by the more ecologically valid inclusion criteria, this study will thoroughly characterise psychiatric comorbidities and medical histories at baseline, so as to be able to distinguish whether treatment responses vary between presentations. Use of the gold standard CAPS-5 PTSD diagnostic tool will also enable the study to characterise trauma histories, and establish whether treatment responses differ between trauma types. This is particularly important, given that PTSD symptom severity and treatment response rates may differ between those with a history of prolonged developmental trauma and those with combat related PTSD [43–46].

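### The only biomarker analysis the article names, a correlation of marker change with response, cannot by itself attribute marker change to NAC; a between-arm comparison should be stated and conclusions kept to the markers measured

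*Protocol article*

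**What the plan says.** The Abstract (Methods) and Study objectives give the blood markers a mechanistic purpose. The Abstract (Discussion) is more cautious, but still speaks of "Inclusion of blood analyses to assess potential target engagement biomarkers of oxidative stress and neuroinflammation".

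Methods, Outcomes makes blood sampling elective at baseline and week 12, calls the markers exploratory, and names one analysis: "Modulation of these blood-based proteins will be correlated with treatment response". It does not say whether the arms are pooled, whether arm is adjusted for, or how response is defined. The Statistical analysis section sets out the CAPS-5 model and describes no biomarker analysis.

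The panel in Table 2 is "IL-6, TNF-alpha, TBARS, MDA, BDNF". The Background builds its rationale on glutathione, and the Discussion says that of key interest is NAC's "ability to replenish glutathione and thereby diminish oxidative stress and neuroinflammation". Glutathione itself is not among the assays.

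**The concern.** A mechanistic question in a randomised trial starts with whether the drug moved the marker, and the comparison of arms answers that. A correlation between marker change and symptom change answers a different question: whether the two move together across participants. A marker that falls whenever people recover, for any reason, will correlate with response in both arms even if NAC leaves it untouched. Conversely, NAC may shift a marker by a similar amount in all treated participants and leave little correlation to find.

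If the correlation were reported alone, a positive result could be read as evidence of mechanism, and a null result as evidence that NAC missed its target. Neither reading would be safe. Separately, the first link in the stated chain, replenishment of glutathione, would have no data behind it.

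**Working it through.** **The plan's own figure.** The only sample size given concerns CAPS-5, for a "true difference in CAPS-5 scores between the NAC and placebo groups of 10+/− 20 points". Reading 20 as the standard deviation, with two-sided alpha 0.05 and 80% power:

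n per arm = 2 × (1.960 + 0.842)² × (20/10)² = 62.8, so 63 per arm and 126 in total, as stated. Inflating for one-third attrition gives 126 / (1 − 1/3) = 189, against 190 stated. The figure reproduces. No figure is given for the biomarkers. I take 126 as the number of paired samples if every target completer gives both.

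**Assumptions for the marker check.** The documents give none of these values.
- Response is CAPS-5 change, and the correlation pools the arms.
- Marker change and CAPS-5 change correlate at r = 0.2 or 0.3 within each arm.
- Paired samples number 60, 90 or 126.

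**Case 1: NAC has no effect on the marker.** The chance that the pooled correlation is significant at two-sided 0.05 is about Φ(atanh(r) × √(n − 3) − 1.96), where atanh(0.2) = 0.2027 and atanh(0.3) = 0.3095.

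| Pairs | r = 0.2 | r = 0.3 |
|---|---|---|
| 60 | 0.33 | 0.65 |
| 90 | 0.47 | 0.82 |
| 126 | 0.61 | 0.93 |

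For example, with n = 60 and r = 0.2: 0.2027 × √57 = 1.53; 1.53 − 1.96 = −0.43; Φ(−0.43) = 0.33.

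A simulation with 63 per arm, r = 0.3 and 5,000 runs agrees. The correlation was significant in 93% of runs with no CAPS-5 effect, and in 91% with a CAPS-5 effect of 0.5 SD. A between-arm test of the marker rejected in about 5% of the same runs, as it should when NAC does nothing to the marker.

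**Case 2: NAC shifts the marker by 0.5 SD, with no within-arm correlation.** With no CAPS-5 effect, the simulated correlation was significant in 5% of runs and the between-arm test in 79%. If NAC also improves CAPS-5 by 0.5 SD, the arms alone induce a pooled correlation of (0.5 × 0.5 × 0.25) / (1 + 0.5² × 0.25) = 0.0625 / 1.0625 = 0.059. With 126 pairs, 0.059 × √123 = 0.65 and Φ(0.65 − 1.96) is about 0.10. The correlation would usually miss the effect.

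**What a between-arm comparison could detect.** Sampling is optional, so power depends on uptake. For an assumed marker effect of 0.5 SD, power = Φ(0.5 × √(k/2) − 1.96), with k pairs per arm. The effect detectable with 80% power is 2.802 × √(2/k).

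| Assumed uptake | Pairs per arm | Power at 0.5 SD | Detectable effect (SD) |
|---|---|---|---|
| 100% | 63 | 80% | 0.50 |
| 75% | 47 | 68% | 0.58 |
| 50% | 31 | 50% | 0.71 |
| 25% | 15 | 28% | 1.02 |

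**Panel against rationale.** The Discussion's chain runs from glutathione replenishment to reduced oxidative stress and neuroinflammation. TBARS and MDA address oxidative stress; IL-6 and TNF-alpha address inflammation. No assay addresses glutathione.

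**The case against.** The strongest reply is that the article condenses a fuller protocol, and the model for an optional, exploratory marker is commonly left to that document or to the SAP. A reader might infer that the correlation replaces a comparison of arms. The text does not say so: it first lists the markers as exploratory outcomes of a randomised trial and then adds the correlation. Nor does it say that the arms are pooled. A within-arm or arm-adjusted correlation would be close to the second analysis proposed below. All of this stands, and it is why the pooled figures are conditional.

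It is also fair that the 33% to 93% are not false-positive rates for the question a correlation asks. By assumption the correlation exists, and the test finds it. The harm arises only if that result is read as an effect of NAC on the marker.

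A reader might further infer that the panel cannot inform mechanism at all, or that the target-engagement wording must go. The documents do not support either. The panel covers the downstream effects in the stated chain, and the Abstract attaches the target-engagement wording to oxidative stress and neuroinflammation, not to glutathione. The planned paired samples also allow a comparison of arms.

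What the reply does not remove is that the article names one analysis for a mechanistic aim, that this analysis alone cannot serve the aim, and that no analysis plan can draw a glutathione result from the stated panel.

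**Conclusion.** The point holds as a cheap improvement to an exploratory analysis. The one biomarker analysis named does not, on its own, tell the reader whether NAC changed a marker. If it ignores arm, it would be significant in 33% to 93% of trials in which NAC has no effect on the marker, and it can miss a real effect of 0.5 SD that a between-arm test would find in 79% of trials with 63 pairs per arm. These sizes rest on assumed correlations, numbers of pairs, effect sizes and pooling. The qualitative point needs only that the correlation ignores arm.

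The absence of glutathione limits what can be concluded about the first link in the chain, not about the downstream markers. Table 2 lists the markers under secondary outcomes while the Outcomes section calls them exploratory; that is a clerical mismatch and adds no weight. The primary CAPS-5 conclusion is unaffected.

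**What to change.** State in the Outcomes or Statistical analysis section, before unblinding:

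- Each of the five markers will be compared between arms at week 12, adjusted for its baseline value, for example by ANCOVA, on the log scale if skewed.
- Marker change will be related to CAPS-5 change with treatment arm in the model. This remains an association, since marker change is not itself randomised.
- Both analyses are exploratory; align the Table 2 label.
- Mechanistic conclusions are limited to the downstream oxidative-stress and inflammatory markers, with no claim about glutathione itself. The target-engagement wording for the downstream markers may stay.

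The cost is a few lines of text, with no new visits, samples or assays. The downsides are a narrower mechanistic claim and limited power for the between-arm comparison because sampling is optional (50% for a 0.5 SD effect if half of the target completers give both samples). The report should therefore give estimates with confidence intervals and the number of pairs per arm.

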### Participant safety and withdrawal

Adverse effects will be assessed each week and reviewed by the study team as well as the Data Safety Monitoring Board, comprising the investigators. Though serious adverse events with NAC are extremely rare, patients will be advised to seek appropriate emergency medical help in such an instance. For less serious events, participants will be advised to contact their treating physician as usual. Participants will be withdrawn from the trial under the following conditions: (i) failure to take the trial medication for seven consecutive days; (ii) cessation of effective contraception or pregnancy; and (iii) withdrawal of consent or emergence of adverse events (as determined by the medical investigators or decision of the participant). All data will be retained in the intention-to-treat analysis.

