### Screening phase and baseline assessment

Individuals with PTSD who express interest in participating in the study will be contacted by a trial clinician and screened according to the eligibility criteria outlined in Table 1 via a brief telephone interview.

After initial telephone screening, eligible participants will be invited to a face-to-face or videoconference 90-min clinical interview. After obtaining IRB-approved written informed consent, a diagnosis of PTSD will be confirmed through the Clinician-Administered PTSD Scale for DSM-5 (CAPS-5) – monthly version, which is the gold-standard in PTSD assessment. Participants will be excluded if they do not meet diagnostic criteria for current PTSD. If patients are deemed eligible and are enrolled in the study, this interview will constitute part of the baseline assessment.

The baseline assessment will also include data collection via clinician-administered and self-reported questionnaires regarding psychiatric comorbidities, PTSD symptoms, quality of life, substance use and somatic symptoms (see Table 2). Detailed clinical and demographic information will be collected on all participants at the baseline clinical interview. This will include age, gender, marital status, years of formal education, service history, receipt of state benefits, ethnicity, and country of birth.

**Table 2 Tab2:** Primary and secondary outcomes according to time-point

Outcome	Measure	Trial							Post-trial		
		Baseline	W 1–3	W 4	W 5–7	W 8	W 9–11	W 12	W 13–15	W 16	W 64

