**Other Measures**											
*Other psychiatric comorbidities*	**MINI V 5.0** (Semi-structured interview to assess habitual substance use and psychiatric comorbidities, including psychotic disorders) [37]	X									
*Demographic Information*	Questionnaire	X									
*Adverse effects*	Self-report			X		X		X			

Indicates clinical interview

Participants will be provided with a signed copy of their information and consent form which includes written information regarding study protocol, purpose, data handling, participant confidentiality, potential side-effects and their right to withdraw from the study at any time.

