### Follow-up assessments

Following baseline assessment and enrolment in the trial, participants will be assessed with clinical interviews at weeks 4, 8 and 12 of the trial. Post-trial interviews are conducted at 16 weeks and 64 weeks to assess retention of any treatment effects. At each follow-up assessment, clinician-rated PTSD symptoms, and self-reported PTSD symptoms as well as psychiatric comorbidities, quality of life, substance use and somatic symptoms are assessed (see Table 2). In between follow-up interviews (from Baseline to Week 16), participants will complete weekly self-report questionnaires regarding their PTSD symptoms. Follow-up interviews will take about 60 min to complete; the weekly self-report questionnaire take approximately 5 min.

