### Standardised medical care

Standard care for participants will involve their regular, medical appointments at variable intervals. The additional procedures involve meeting with the research clinician in outpatients of the clinical services – where possible to coincide with scheduled appointments – at 4-weekly intervals, where they will engage in a clinical interview, and complete self-report questionnaire items. Participants will also be asked to complete one self-report questionnaire, each week on their own.

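### The text has adverse effects assessed weekly, but Table 2 schedules them only at weeks 4, 8 and 12, and no weekly instrument for them is described

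*Protocol article*

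**What the plan says.** Three parts of the protocol article bear on how often adverse effects are collected.

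- **Participant safety and withdrawal.** The frequency is weekly: "Adverse effects will be assessed each week and reviewed by the study team". The same sentence gives the Data Safety Monitoring Board a part in the review. Withdrawal follows seven consecutive days without trial medication, among other conditions, or the emergence of adverse events.
- **Table 2** (under Screening phase and baseline assessment). The time-point columns read "Baseline W 1–3 W 4 W 5–7 W 8 W 9–11 W 12 W 13–15 W 16 W 64". The row labelled "Adverse effects", under Other Measures, gives self-report as the method and is marked at weeks 4, 8 and 12 only.
- **The weekly contact.** Follow-up assessments says that between interviews "participants will complete weekly self-report questionnaires regarding their PTSD symptoms". Standardised medical care adds: "Participants will also be asked to complete one self-report questionnaire, each week on their own". Clinical interviews during treatment are at weeks 4, 8 and 12.

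The Outcomes section makes self-report the basis of the safety evaluation: "The safety and tolerability of the intervention will be evaluated by self-report".

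**The concern.** The article gives two frequencies for the same data item, both in current text. Because safety and tolerability rest on self-report, the self-report schedule determines the safety data set. A site working from Table 2 would not collect what the safety section says is reviewed each week.

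Two things would be lost. Effects that come and go between 4-weekly interviews would depend on what participants still report at the next interview. And the study team and the monitoring board would have no new scheduled data in nine of the twelve treatment weeks. Participants who leave before the first interview are the sharpest case, because their data cannot be collected afterwards. A later analysis plan cannot repair this, since it can only analyse what sites recorded.

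**Working it through.** **1. Is the Table 2 row read correctly?** The header has ten time-point columns and the adverse-effects row has ten time-point cells, so the row has not shifted in the reading of the PDF. Cell by cell:

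| Time-point | Adverse effects | PCL-5 |
|---|---|---|
| Baseline | – | X |
| W 1–3 | – | X |
| W 4 | X | X |
| W 5–7 | – | X |
| W 8 | X | X |
| W 9–11 | – | X |
| W 12 | X | X |
| W 13–15 | – | X |
| W 16 | – | X |
| W 64 | – | X |

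The table has separate columns for the weeks between visits and uses them for the PCL-5. It can therefore show weekly collection, and for adverse effects it does not.

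**2. Count over treatment (weeks 1 to 12).**

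- Text: one assessment a week gives 12.
- Table 2: weeks 4, 8 and 12 give 3.
- Difference: 12 − 3 = 9 weeks (1, 2, 3, 5, 6, 7, 9, 10, 11) covered by the text and not by the table.

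**3. Does anything else described supply weekly adverse-effect data?**

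- PCL-5: the only measure marked in the between-visit columns; a PTSD symptom scale.
- Daily pill diary (Allocation): described as a record of compliance.
- Meetings with the research clinician (Standardised medical care): every four weeks.
- The Abstract's statement that self-report measures are completed weekly: this does not help, because Table 2 marks only the PCL-5 weekly.

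None is described as collecting adverse effects.

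**4. How many could leave before the first Table 2 collection at week 4?** The input is the sample size section: one-third attrition and 190 recruited for 126 completers. The plan's figure reproduces: 126 / (1 − 1/3) = 189, against 190 stated. The expected loss is 190 / 3 ≈ 63.

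The timing of loss is not given. That section counts completers of both trial and follow-up, and follow-up assessments run to week 64. Assuming, for illustration only, loss at a constant rate over a horizon of H weeks, the number leaving before week 4 is 63 × 4 / H:

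| Horizon H (assumed) | Calculation | Leavers before week 4 | Share of 190 |
|---|---|---|---|
| 64 weeks | 63 × 4/64 = 3.9 | about 4 | 2% |
| 16 weeks | 63 × 4/16 = 15.8 | about 16 | 8% |
| 12 weeks | 63 × 4/12 = 21 | 21 | 11% |

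Loss concentrated early would give more than the row for its horizon. The contradiction in steps 1 to 3 does not depend on any of these figures.

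**The case against.** The strongest reply is that the safety section is the dedicated statement on adverse effects and that Table 2 is captioned as a table of primary and secondary outcomes. If the text governs, participants who leave early do have weekly records. This stands as far as it goes: the consequence for early leavers is conditional on Table 2 being operative. It does not remove the contradiction, because Table 2 carries an explicit adverse-effects row with its own time-points.

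A second reply is that an article need not reproduce the weekly form, so an adverse-effects question may be on it. That is possible, and a reader should not infer that the form certainly lacks one. The article shows only that the weekly form is described by its PTSD content and that Table 2 leaves the between-visit cells for adverse effects blank. Detail left to a full protocol would excuse silence, but here two stated schedules conflict.

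Third, a reader might infer that people who leave because of adverse events go unrecorded. The documents do not support that. An adverse event is a listed ground for withdrawal, as determined by the medical investigators or decided by the participant, so the team may well know of it. What the article lacks is a scheduled point for recording it. Nor is any recall period for adverse effects stated, so under-reporting from long recall is a plausible risk and not something the plan fixes.

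**Conclusion.** The inconsistency is certain: weekly in the text, weeks 4, 8 and 12 in Table 2, or 12 against 3 collections over treatment, with no weekly instrument for adverse effects described. It should be corrected, because it decides what safety data exist.

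The consequence is conditional. If Table 2 is the operative schedule, the weekly review has no described data source, and those who leave before week 4 have no scheduled adverse-effect record. Later leavers lack scheduled coverage only since their last 4-weekly interview.

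A reader might infer that about 21 people, 11% of those recruited, would be affected. The documents do not support a single figure. That one puts all the attrition into 12 weeks, whereas the plan defines it over trial and follow-up. Under uniform loss the range is about 4 to 21, and the true number cannot be computed without attrition timing.

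The primary outcome, sample size and mixed-model analysis are not touched.

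**What to change.** Reconcile the safety section with the adverse-effects row of Table 2, so that one frequency is stated in both, and name the instrument that collects adverse effects.

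If the weekly assessment in the text is what is intended, it can be delivered without a new visit: add an adverse-effects item to the weekly form that participants already complete (about 5 minutes, per Follow-up assessments), and mark the W 1–3, W 5–7 and W 9–11 cells in Table 2. If the Table 2 schedule is intended, the safety section needs rewording, including what is reviewed in the weeks between interviews.

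The cost is a text and table edit and, for weekly collection, slightly more participant time and data entry.

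Recording adverse effects at early withdrawal and at the existing week-16 interview is an optional addition. It would close the gap for early leavers, but the contradiction does not require it.

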**Methods:**

A multicentre, randomised, double-blind, placebo-controlled trial for adult patients who still meet criteria for PTSD following first-line treatment. The intervention comprises either NAC as a fixed dose regime of 2.7 g/day (900 mg three times daily) administered orally for 12 weeks, or placebo. Standard care for PTSD will continue in addition, including other pharmacotherapies. Detailed clinical data will be collected at randomisation and weeks 4, 8, 12, 16, and 64 post-randomisation, with self-report measures completed weekly from baseline to 16 weeks and at 64 weeks post-randomisation. Blood-based biomarkers will be collected at baseline and 12 weeks to assess the mechanism of effect. The primary outcome measure will be change in Clinician-Administered PTSD Scale for DSM-5 at 12 weeks compared with baseline. Secondary outcomes will be change in quality of life, depression, anxiety, substance use and craving, and somatic symptoms. With 126 completed participants (63 per arm), the study is powered at 80% to detect a true difference in the primary outcome measure using a two-tailed analysis with alpha = 0.05, beta = 0.2.

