### Statistical analysis

All analyses will be conducted by our independent trial statistician and will include all randomised participants with at least one post-baseline observation (modified intention to treat). The statistician will be blind to group allocation (triple blind design). Differences between study arms at baseline will be assessed using either chi-squared or Fisher’s exact test for categorical data and either student t–test or Mann-Whitney U test for continuous data. Non-parametric statistics will be used when assumptions for parametric methods are violated. Effect sizes will be calculated using Cohen’s guidelines. The primary efficacy analysis will assess the impact of the treatment on group differences for the primary outcome measure (CAPS-5) over the entire study period and use a likelihood based mixed-effects model, repeated measures approach (MMRM). The MMRM model includes the categorical effects of treatment, investigator, visit, and treatment-by-visit interaction, as well as the continuous, fixed covariates of baseline score and baseline score-by-visit interaction.

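### Seven missed days or adverse events remove a participant from the trial, not only from study drug, so on the plain reading outcomes after withdrawal, including week 12, are not collected for the promised intention-to-treat analysis

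*Protocol article*

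**What the plan says.** All references are to the protocol article.

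- **Participant safety and withdrawal.** "Participants will be withdrawn from the trial under the following conditions: (i) failure to take the trial medication for seven consecutive days". Item (ii) covers stopping contraception and pregnancy. The last item joins two different events: "iii) withdrawal of consent or emergence of adverse events (as determined by the medical investigators or decision of the participant". All of them lead out of the trial; none is described as stopping study medication only. The paragraph ends: "All data will be retained in the intention-to-treat analysis".
- **Follow-up assessments and Table 2.** There is one visit schedule: "participants will be assessed with clinical interviews at weeks 4, 8 and 12 of the trial", then weeks 16 and 64. No assessment is described for someone who has been withdrawn.
- **Abstract, Methods.** "The primary outcome measure will be change in Clinician-Administered PTSD Scale for DSM-5 at 12 weeks compared with baseline".
- **Statistical analysis.** The analyses "will include all randomised participants with at least one post-baseline observation (modified intention to treat"). The primary analysis will "use a likelihood based mixed-effects model, repeated measures approach (MMRM").
- **Sample size calculation and recruitment target.** "Using a conservative attrition rate of one-third, we will need to recruit 190 participants"; the attrition is counted over the trial and follow-up together.

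**The concern.** An intention-to-treat comparison needs the outcomes of everyone randomised, whether or not they kept taking the drug. Retaining the data in hand does not supply data that were never gathered. The rule treats a participant who stops medication but would still attend interviews in the same way as one who refuses further contact. The plan would thereby create missing week-12 values itself, and among the people who take or tolerate the medication poorly.

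The model does not repair this. The MMRM assumes that, given baseline and earlier scores, the unseen values behave like those of same-arm participants who remain, and these are largely people still on drug. If stopping changes the later course in a way that earlier scores do not predict, the estimate moves towards the effect under continued treatment. Adverse-event follow-up may also end for those withdrawn because of adverse events.

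The first post-baseline CAPS-5 is at week 4. Someone withdrawn before then contributes no post-baseline data on the primary outcome, although a weekly PCL-5 might count as a post-baseline observation. The two sections also name different analysis populations, intention-to-treat and modified intention-to-treat.

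**Working it through.** **1. Reproduce the plan's figures.** Inputs from the sample size section: difference 10, SD 20 (reading 10 ± 20 that way), two-sided alpha 0.05, power 80%. The 1:1 ratio is from Allocation.

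- Per arm: n = 2 × (1.960 + 0.842)² × (20/10)² = 62.8, so 63, and 126 in total. Power at 63 per arm is 80.1%.
- Attrition of one-third: 126 / (1 − 1/3) = 189, against 190 stated.

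The figures reproduce to within one participant. At the planned attrition, 190 − 126 = 64 participants (34%) do not complete. The plan does not say how many of these would fall under the seven-day or adverse-event rules, or by which week.

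**2. Effect with and without outcomes after stopping.** Assumptions, none given in the documents:

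- a fraction q of the NAC arm stops before week 12 under these rules;
- those who stop keep a fraction k of the benefit;
- stopping placebo changes nothing;
- earlier scores do not predict the loss of benefit, so an MMRM without later data still targets about 10 points.

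Effect in all randomised = 10 × (1 − q) + 10 × k × q. Overstatement = 10 minus that value.

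| q | k | Effect, all randomised | Overstatement | As % of that effect |
|---|---|---|---|---|
| 10% | 0 | 9.0 | 1.0 | 11% |
| 20% | 0 | 8.0 | 2.0 | 25% |
| one-third | 0 | 6.7 | 3.3 | 50% |
| 10% | 0.5 | 9.5 | 0.5 | 5% |
| 20% | 0.5 | 9.0 | 1.0 | 11% |
| one-third | 0.5 | 8.3 | 1.7 | 20% |

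The one-third row is an upper bound, since that figure is attrition from all causes.

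**3. Power if everyone is followed.** With 190/2 = 95 per arm and SD 20, the standard error is 20 × √(2/95) = 2.90, and power is Φ(effect/2.90 − 1.96).

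- k = 0: 87%, 79% and 63% for q of 10%, 20% and one-third.
- k = 0.5: 91%, 87% and 82%.

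In the extreme case (6.7 points), 80% power needs 2 × (2.802)² × (20/6.67)² ≈ 141.3, so 142 per arm.

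**The case against.** Several points on the other side are sound.

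- **No sentence says that visits stop.** The article is condensed, and the full protocol may describe follow-up after discontinuation. In Table 2 the word trial heads baseline to week 12, and later visits are headed post-trial, so leaving the trial need not cancel weeks 16 and 64. A reader might infer that every assessment to week 64 is lost; the text does not establish that. It does not rescue week 12, which lies inside the trial period even on that narrower meaning.
- **Withdrawn participants are not dropped.** A reader might infer that the analysis lacks their outcomes altogether. It does not: CAPS-5 scores from before withdrawal enter the likelihood, and a poor early response is partly conditioned on.
- **The one-third is not q.** It covers loss from all causes through follow-up and is called conservative. It includes refusals, which no change of wording would recover.
- **Zero retained benefit is an assumption.** The Discussion reports mixed findings on whether NAC effects last after treatment in other disorders.
- **The direction is not fixed.** Loss that differs by arm could bias either way.

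These points limit the certainty and the size. They do not remove the problem, because the article states a rule rather than merely leaving one out. No later analysis plan can analyse assessments that were not made. If continued follow-up is intended, the present wording says otherwise and needs the same amendment.

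**Conclusion.** The concern holds in limited form. Followed as written, the rule makes stopping medication equivalent to leaving the trial. On the plain reading this leaves the week-12 CAPS-5 uncollected for reasons tied to adherence and tolerability. The primary analysis then approximates the effect under continued treatment, which is not the intention-to-treat effect promised.

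The illustrated overstatement is 1.0 to 3.3 points with no retained benefit and 0.5 to 1.7 points with half retained, for q from 10% to one-third. It rests on a 10-point on-drug effect and on the assumptions in the working. It would be wrong to read 3.3 points, or 50%, as the expected bias: the documents give neither q nor the benefit kept. The point still matters before analysis, because week-12 outcomes that are not collected cannot be recovered afterwards.

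**What to change.** Leave the criteria for stopping study medication exactly as they are. Add that meeting one of them does not end trial participation. Participants continue the CAPS-5, self-report and adverse-event assessments already scheduled unless they withdraw consent to follow-up, and these data enter the primary analysis. Record stopping medication and withdrawing consent to follow-up as separate events with separate dates. Reconcile the intention-to-treat wording under Participant safety and withdrawal with the modified intention-to-treat set under Statistical analysis.

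The cost is a short amendment and visits for people no longer on drug. The visits are on the existing schedule; the documents do not show their funding. The estimated effect may be smaller, and power for it may fall below 80% if many stop and keep little benefit (79% and 63% in the 20% and one-third cases above). The change helps only participants whose visits still lie ahead.
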